### Blinding

The study is presented to the patients to study whether light therapy would be a beneficial treatment modality for major depressive disorder. The blue light and red light conditions are presented to study whether a specific part of the light spectrum would be more effective than another.

Light treatment is blinded to the investigators as the lamps are delivered at the patient's homes by a specially trained protocol blinded instructor, so the instructors are led to believe that the blue and red light conditions are to study which part of the spectrum worked better than the other.

The patients are asked not to refer any details of their condition to the investigators as this would harm the study. When patients however do reveal their condition, the researcher will be replaced immediately by another researcher to perform psychometrical interviewing and ratings.

To evaluate the blinding procedure, and in order to assess participants' general expectations for light therapy and their specific expectations in respect to their allocated light boxes, we measure expectations before the light box was installed using a four item expectations questionnaire. Briefly, participants rate, on a 7-points scale (1 = feeling much better, 2 = feeling definitely better, 3 = feeling slightly better, 4 = no change, 5 = feeling slightly worse, 6 = feeling definitely worse, 7 = feeling much worse), how they thought light therapy would improve their symptoms. We use four questions to be rated: (1) To what extent do you expect your problems will improve without treatment? (2) To what extent do you expect your problems will improve with light treatment? (3) To what extent do you expect your problems will improve with the blue light treatment? (4) To what extent do you expect your problems will improve with the red light treatment?

### Statistical analysis

Data will be analyzed using SPSS 16.0. Analyses are performed using intention-to-treat principles. Therefore, drop-outs are distinguished into 'drop-outs before T1 assessment' and 'drop-outs after T1 assessment'. When only a randomisation assessment (T0) is available, subjects are considered lost to follow-up. For 'drop-outs after T1 assessment' the principle of LOCF (last observation carried forward) will be used. For sensitivity analysis, the more conservative LOCF variant will be calculated where T0-data will be carried forward, and a completers analysis will be performed.

Baseline characteristics across the treatment groups are compared using analysis of variance (ANOVA) and χ^2^-statistics.

As the primary analysis efficacy of treatment is tested by performing a repeated measures analysis of variance (RMANOVA) on HADRS-17 scores at T0, T1 and T2. To control for possible difference in baseline severity scores baseline values for HADRS-17 are used as covariates. Repeated contrasts are applied to compare effects in the treatment period with effects after the treatment period. As secondary analyses efficacy of treatment is tested by performing RMANOVA on the other depression symptom scales (SIGH-SAD scores, HAM-D6, MADRS-scores). As tertiary analyses depression outcome measures are dichotomised to responders and non-responders, where response is defined as a decrease of ≥ 50% on the HADRS-17, HAM-D6, SIGH-SAD and MADRS scales. Responder rates will also be presented as odd's ratios and NNT's.

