### Sample size

Martiny et al. [21] found a moderate effect size (ES>0,50 maximum 0,66) for bright light treated group in comparison with dim light treated group on both self-assessment and observer rating scales in patients with a high prevalence of melancholic depression. Based on the literature on the expected response rate, and using conventional values for α (0.05) and β (0.80), and two-tailed tests with equal groups, the sample size aimed for in the current study is 63 patients per arm [42].

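### Carrying T0 forward in both arms is conservative for bright light only if active-arm dropout is about equal to or higher than placebo dropout; the protocol states the label without that condition

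*Protocol article*

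**What the plan says.** All of the missing-data rules stand in the Statistical analysis section of the protocol article.

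- Patients with a baseline value only: "When only a randomisation assessment (T0) is available, subjects are considered lost to follow-up".
- Patients who leave later: "For 'drop-outs after T1 assessment' the principle of LOCF (last observation carried forward) will be used".
- First sensitivity analysis: "For sensitivity analysis, the more conservative LOCF variant will be calculated where T0-data will be carried forward".
- Second sensitivity analysis: "and a completers analysis will be performed".

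The primary model to which these apply is a "repeated measures analysis of variance (RMANOVA) on HADRS-17 scores at T0, T1 and T2", with baseline HADRS-17 as a covariate.

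Two things are left open. The label on the first sensitivity analysis is a comparison with ordinary LOCF, but nothing says under what pattern of dropout the comparison holds. Nor does the text say whether T0 is carried forward for every drop-out, including those with a baseline value only, or just replaces T1 as the carried value for those who leave after T1. No dropout rate is given.

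**The concern.** Carrying T0 forward is conservative for the single patient, because a drop-out is credited with no improvement. The efficacy analysis, however, compares arms. When both arms improve, as is usual in depression trials, each placebo drop-out set to zero change lowers the placebo mean, just as each active drop-out lowers the active mean. Which arm loses more depends on which has more drop-outs, and that is unknown when the plan is written.

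This and the completers analysis are the only checks on missing data that the article names. If placebo loses more patients, the check labelled conservative may favour bright light more than the primary analysis does. A reader who trusts the label could then take agreement between the two as evidence of robustness.

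**Working it through.** **Inputs from the document.** Sample size section: "using conventional values for α (0.05) and β (0.80), and two-tailed tests with equal groups"; "found a moderate effect size (ES>0,50 maximum 0,66"; "the sample size aimed for in the current study is 63 patients per arm". Background, on nonseasonal depression: 40.7% response under dim red light in the cited sertraline-adjunct trial, so control-arm improvement is expected.

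**Inputs assumed.** Dropout by arm; common improvement of 5 or 8 HADRS-17 points; mean 18 at T0; SD 4 at T0 and 6 at T1 and T2; correlations 0.4 (T0 with later visits) and 0.7 (T1 with T2); dropout unrelated to outcome unless stated. The model is a baseline-adjusted comparison of the T1/T2 mean, standing in for the planned RMANOVA.

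**Step 1: the plan's own figure.** Reading the stated 0.80 as power and taking the lower effect size of 0.50, n = 2(1.960 + 0.842)² / 0.50² = 62.8, so 63 per arm. It reproduces and is not in dispute.

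**Step 2: the shift.** Let dA and dP be the dropout proportions, and mA and mP the mean improvements. With zero change for drop-outs, the expected arm difference is

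(1 − dA)·mA − (1 − dP)·mP.

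- No treatment effect (mA = mP = m): the difference is m·(dP − dA). At 10%/20% (active/placebo here and below) and m = 8, it is 0.10 × 8 = 0.8 points toward bright light.
- True effect δ (mA = mP + δ): the difference is δ − dA·δ + (dP − dA)·mP. It exceeds δ once (dP − dA)·mP is greater than dA·δ. The label therefore survives a small placebo excess when the effect is real, and survives none when it is not.

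**Step 3: a 3-point true effect, placebo improvement 8, active 11, T0 replacing T1 and T2.**

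| Dropout active/placebo | Calculation | Estimate |
|---|---|---|
| 10%/20% | 0.90 × 11 − 0.80 × 8 | 3.5 (enlarged) |
| 20%/10% | 0.80 × 11 − 0.90 × 8 | 1.6 (attenuated) |

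If T0 replaces only T2, the T1 half is untouched. The 10%/20% estimate for the T1/T2 mean is then (3.0 + 3.5)/2 = 3.25, and simulation gave 3.2.

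**Step 4: rejection rate with no treatment effect.** Simulation at 63 per arm, two-sided 5%. The ranges span improvements of 5 and 8 points and repeat runs.

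| Dropout active/placebo | T0 replaces T1 and T2, all drop-outs | T0 replaces T2 only, drop-outs after T1 |
|---|---|---|
| 10%/20% | about 9–14% | about 5–7% |
| 10%/30% | about 20–38% | about 8–16% |

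With 15%/15% dropout and T0 replacing both visits, the rate is about 5%. Completers stay at about 4–6% throughout, but that follows from assuming dropout unrelated to outcome.

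**Step 5: comparison with the primary LOCF.** In a T2 simulation with improvement of 8 points at T1 and 9 at T2, 5%/25% dropout, half of it before T1 and no treatment effect, LOCF shifted the difference by 0.11 to 0.14 points and rejected about 5% of the time. Carrying T0 forward shifted it by 1.8 points (38%) for all drop-outs, or 1.07 points (16%) for late drop-outs only. Here the variant is less conservative than the rule it is compared with.

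**Step 6: response.** A patient with T0 carried forward is a non-responder by construction. With 40.7% response in both arms and 5%/25% dropout, the rates become 0.95 × 40.7 = 38.7% and 0.75 × 40.7 = 30.5%. That is a gap of 0.20 × 40.7 = 8.1 points with no effect.

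**The case against.** Five points can be made for the plan.

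1. *The narrow reading is natural.* Patients with T0 only are classed as lost to follow-up, and the rule is introduced as a variant of LOCF, which applies to those who leave after T1. On that reading a 10-point gap barely moves the error rate. This stands, and it is why both readings are shown. The wider one remains possible because the section invokes intention-to-treat.

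2. *Dropout through lack of benefit behaves differently.* If placebo patients leave because they did not improve, zero change is near the truth. With a true 3-point effect and the same benefit-driven dropout rule in both arms (3–17% active, 8–30% placebo), T0 carry-forward gave 2.8 to 3.1 points against 2.4 to 2.7 in completers. This also stands: the bias depends on why patients leave.

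3. *The one arm-specific cause in the document points the other way.* The Adverse effects section calls eye strain characteristic of bright light. That would raise active-arm dropout, where the label is fair. True, but the direction is still not known in advance.

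4. *It is a secondary check.* A completers analysis sits beside it and no decision rule depends on it, so a divergence would be visible. This limits the consequence without making the label correct.

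5. *Imputation detail belongs in an analysis plan.* Agreed, and its absence here is not the criticism. The criticism is of a property that the article states.

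A reader might go further and infer that this analysis will manufacture a benefit, or that it is worthless as a safeguard. The document does not support that: it gives no dropout rates, nothing in it predicts a large placebo excess, and with equal or higher active-arm dropout the analysis does attenuate the effect.

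**Conclusion.** The unconditional label is wrong; the analysis itself can stay as one check among several. It is conservative for bright light when active-arm dropout is about equal to or higher than placebo dropout. When placebo loses more for reasons unrelated to outcome, the shift favours bright light by about the gap times the common improvement, or about half that for the T1/T2 mean if only T2 is replaced.

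The effect on the error rate is modest at a 10-point gap and becomes large near 20 points only if T0 replaces both visits for all drop-outs. The algebra needs no outside figure. The percentages rest on assumed dropout, improvement, SDs and correlations, and on a baseline-adjusted T1/T2 mean in place of the planned RMANOVA. The point does not touch the sample size, and it is not a criticism of the primary LOCF of T1 into T2. It should be corrected before the analysis, but it does not threaten the trial.

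**What to change.** In the Statistical analysis section:

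1. Remove the claim of conservatism, or limit it to the case where active-arm dropout is at least that of placebo.
2. State which drop-outs receive T0 (all, or only those who leave after T1) and which visits it replaces.
3. Report dropout by arm, with timing, next to the result.
4. Add a sensitivity analysis whose direction is fixed against bright light. One form is multiple imputation with a delta penalty added to active-arm drop-outs, raised until significance is lost, with the tipping value reported.

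The cost is a change of wording and a little more analysis, with no new patients or data. The sensitivity result may turn out less favourable to bright light.

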**Methods/Design:**

This study aims to show whether BLT can reduce non-seasonal major depression in elderly patients. Randomized double blind placebo controlled trial in 126 subjects of 60 years and older with a diagnosis of major depressive disorder (MDD, DSM-IV/SCID-I). Subjects are recruited through referrals of psychiatric outpatient clinics and from case finding from databases of general practitioners and old-people homes in the Amsterdam region. After inclusion subjects are randomly allocated to the active (bright blue light) vs. placebo (dim red light) condition using two Philips Bright Light Energy boxes type HF 3304 per subject, from which the light bulbs have been covered with bright blue- or dim red light- permitting filters. Patients will be stratified by use of antidepressants. Prior to treatment a one-week period without light treatment will be used. At three time points several endocrinological, psychophysiological, psychometrically, neuropsychological measures are performed: just before the start of light therapy, after completion of three weeks therapy period, and three weeks thereafter.

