### Primary Outcome measure

Depression severity is assessed by a trained research physician and qualified research psychologists (MN, [name]) using the Montgomery-Åsberg Depression Rating Scale (MADRS) [44], the combined 21-item Hamilton and 8-item atypical symptom scales of the Structured Interview Guide for the Hamilton Depression Rating Scale – Seasonal Affective Disorder Version (SIGH-SAD) [45], which although originally designed for SAD studies is equally applicable for assessment of nonseasonal depression with atypical features (as in the present study). The Hamilton and atypical symptom subscales of the SIGH-SAD can be analyzed separately or in combination [46]. The primary outcome measure is depression ratings using the HADRS-17 scale. Response is defined as a 50% reduction in depressive symptoms, on the HADRS-17 scale at T1 and T2. Specially trained clinical research staff conducts the interview.

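### The primary RMANOVA uses the T0 HADRS-17 score as both outcome and covariate, so its overall arm effect is two thirds of the true post-baseline effect; no deciding term is named

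*Protocol article*

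**What the plan says.** The Primary Outcome measure section names the variable: "The primary outcome measure is depression ratings using the HADRS-17 scale". The Statistical analysis section makes the primary analysis a repeated measures ANOVA on "HADRS-17 scores at T0, T1 and T2. To control for possible difference in baseline severity scores baseline values for HADRS-17 are used as covariates".

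T0 is that baseline. The abstract's Methods/Design paragraph places the three assessments "just before the start of light therapy, after completion of three weeks therapy period, and three weeks thereafter", and the Statistical analysis section treats T0 as the assessment at randomisation: "When only a randomisation assessment (T0) is available, subjects are considered lost to follow-up".

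On contrasts, the plan says: "Repeated contrasts are applied to compare effects in the treatment period with effects after the treatment period". No sentence states which RMANOVA term, or which visit, decides whether the treatment worked. The responder definition ("Response is defined as a 50% reduction in depressive symptoms, on the HADRS-17 scale at T1 and T2") gives no order between the visits either, but it concerns a dichotomised outcome that the analysis section ranks as tertiary, so it does not settle the matter.

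**The concern.** A score cannot usefully be an outcome and its own covariate. Once T0 is regressed on T0, nothing is left at that level: no residual and no arm difference. Averaging that empty level with T1 and T2 shrinks the overall arm effect. If that line is reported as the treatment effect, readers and meta-analysts receive a figure that is too small, with an interval that is too narrow as a statement about the post-baseline effect.

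The second problem is separate. The RMANOVA prints a group effect, a group-by-time effect and two adjacent-visit contrasts, and these answer different questions. If the deciding line is chosen after the results are seen, the nominal 5% no longer holds.

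**Working it through.** **Inputs.** From Sample size: two-sided alpha 0.05, power 0.80 (printed there as β), equal arms, a cited effect size above 0.50 (maximum 0.66), 63 per arm. From Statistical analysis: outcome levels T0, T1, T2, with T0 as covariate. The document gives no correlations between visits, so those below are assumptions.

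**The plan's own figure.** n per arm = 2 × (1.960 + 0.842)² / 0.50² = 62.8, rounded up to 63. The stated sample size is reproduced at an effect of 0.50 SD, which therefore serves as the yardstick.

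**Overall group effect.** Let d1 and d2 be the baseline-adjusted arm differences at T1 and T2, and M = (T1 + T2)/2. The between-group test works on the mean of the three levels:

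(T0 + T1 + T2)/3 = (1/3)·T0 + (2/3)·M

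Regress this on arm and T0. The covariate absorbs the first term, so:

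- arm coefficient = (0 + d1 + d2)/3 = (2/3) × (d1 + d2)/2
- residual, and hence standard error = 2/3 of that for M
- t, F, p value and power = the same as for M

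With d1 = d2 = 0.50 SD the estimate is 1.00/3 = 0.33 SD instead of 0.50. Relative to T1 alone the ratio is (d1 + d2)/(3·d1): 2/3 for equal effects, and 0.75/1.50 = 1/2 if d2 is half of d1.

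**T0-to-T1 contrast by group.** Regressing T1 − T0 on arm and T0 gives arm coefficient d1 and the same residuals as ANCOVA at T1. This line is correct.

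**Group-by-time.** The two contrasts estimate d1 and d2 − d1. Both are zero only when d1 = d2 = 0, so the 2-df test is a valid test of no effect at either visit.

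**Simulation** (63 per arm, 4000 runs per setting; T1–T2 correlation 0.6, 0.6 and 0.7 for the three columns):

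| Correlation of T0 with T1 and T2 | 0.3 | 0.5 | 0.7 |
|---|---|---|---|
| Estimate, three levels (true 0.50 at both visits) | 0.335 | 0.334 | 0.333 |
| Estimate, T1 and T2 only | 0.502 | 0.500 | 0.500 |
| Power, group effect (same in both models) | 0.909 | 0.964 | 0.995 |
| Power, ANCOVA at T1 (same as T0-to-T1 contrast) | 0.832 | 0.895 | 0.972 |
| Power, group-by-time | 0.869 | 0.921 | 0.987 |
| Rejection, T1-to-T2 contrast | 0.054 | 0.051 | 0.058 |
| Null: group effect | 0.052 | 0.054 | 0.051 |
| Null: group-by-time | 0.054 | 0.054 | 0.058 |
| Null: group or group-by-time | 0.075 | 0.084 | 0.088 |

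The ratio of the two estimates and the ratio of their standard errors were 0.6667 in every simulated data set.

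**Terms can disagree.** With 0.50 SD at T1 and 0.25 SD at T2 (correlations 0.5 and 0.6), the three-level estimate is 0.25 SD. Power is 0.80 for the group effect, 0.83 for group-by-time, 0.91 for T1 and 0.34 for the T1-to-T2 contrast. With 0.50 SD at T1 and none at T2 (0.5 with T0, 0.6-0.8 between T1 and T2), the group effect has 40-47% power and the group-by-time test 91-99%.

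**The case against.** The strongest reply is that the shrinkage sits on one line of output, and the plan never says that line will be the reported effect. The T0-to-T1 contrast is in the same output and is right, and no test loses validity through the double role. All of this stands, and it limits the point to the size of one estimate and the missing choice of term. It does not rescue the model, because the three-level group effect is wrong by a known factor and T0 contributes nothing to it.

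A second reply is that naming the deciding term is commonly left to an analysis plan that is not shown. That is fair as to detail. But the article does fix the primary model, and as fixed it offers several efficacy answers.

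Stronger readings are tempting but unsupported:

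- **The double role costs power.** It does not, because estimate and standard error shrink together. A loss would arise if T0 stayed as a level and the covariate were dropped (0.68, 0.61 and 0.55 against 0.88, 0.87 and 0.86 with T1 and T2 only), but the plan keeps the covariate. The 40-47% above comes from averaging T1 with T2 under an assumed vanishing effect, and a T1/T2 model has the same group-effect power.
- **The group-by-time test wastes a degree of freedom.** It is full rank for d1 = d2 = 0, and its null rejection is 5-6%.
- **The plan has a 12% type I error.** That needs all four lines counted as efficacy tests and one picked afterwards. The plan gives the contrasts their own purpose, comparing the treatment period with the period after it, so the T1-to-T2 contrast is not a mistaken test of T2.

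**Conclusion.** The point holds in limited form. As written, the overall between-group estimate and both its confidence limits are two thirds of the baseline-adjusted T1/T2 mean effect. This is exact algebra and needs no assumed correlation. A trial that achieved its 0.50 SD design effect at both visits would show 0.33 SD on that line. The significance of that line is correct.

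The lack of a named deciding term is the second part. The 7-9% error rate arises only if success may be claimed on either the group or the group-by-time test, and it rests on the assumed correlations. A reader might infer that T1 is the only proper primary visit. The document does not support that, because the trial studies both the treatment period and the three weeks after it.

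**What to change.** Reword one paragraph of the Statistical analysis section:

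- Outcomes are HADRS-17 at T1 and T2. T0 enters as covariate only.
- Add antidepressant use as a factor, since the Randomization section stratifies on it.
- Name one deciding contrast, two-sided 5%, before unblinding. One choice is the adjusted arm difference at T1, the end of treatment, with the T2 difference and the T1-to-T2 contrast as supportive.

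The data and software stay the same, and removing T0 from the outcomes costs no power. Choosing T1 alone has a small price if the effect persists: about 88-90% power against 93-96% for the T1/T2 mean (0.50 SD at both visits, assumed correlations 0.5 with T0 and 0.6-0.8 between T1 and T2). If the effect fades by T2, T1 alone does better. The sponsor may choose either, provided one is fixed in advance.

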### Approval

The current study is executed in accordance with the principles laid down in the Helsinki Declaration [43]. Participation in the study is voluntary, and written informed consent is obtained. The patients are explicitly informed of the fact that they can withdraw their consent to participate at any time, without specification of reasons and with no negative consequences with regard to their future medical treatment. Patients who wish to withdraw from the study will receive care as usual. Approvals were obtained by the Dutch authorities and the medical ethical committee of GGZ Nederland.

### Primary Outcome measure

Depression severity is assessed by a trained research physician and qualified research psychologists (MN, [name]) using the Montgomery-Åsberg Depression Rating Scale (MADRS) [44], the combined 21-item Hamilton and 8-item atypical symptom scales of the Structured Interview Guide for the Hamilton Depression Rating Scale – Seasonal Affective Disorder Version (SIGH-SAD) [45], which although originally designed for SAD studies is equally applicable for assessment of nonseasonal depression with atypical features (as in the present study). The Hamilton and atypical symptom subscales of the SIGH-SAD can be analyzed separately or in combination [46]. The primary outcome measure is depression ratings using the HADRS-17 scale. Response is defined as a 50% reduction in depressive symptoms, on the HADRS-17 scale at T1 and T2. Specially trained clinical research staff conducts the interview.

